### Trial design

This is a feasibility study, which will use an explanatory sequential mixed-methods approach. In this approach, the quantitative aspect forms the first part of the study, followed by a qualitative aspect to help provide further explanation and depth.^32^ For the quantitative aspect, the study will use a parallel, randomised design with an equal proportion of participants allocated to each of the four conditions. The qualitative aspect will be completed by interviewing the participants of the intervention and the practitioner delivering them.

## Methods: participants, interventions and outcomes

### Study setting

The study will take place at Swansea University in South Wales, UK with participants being recruited from both the student population at the university and the general public. The interventions will only take place in one location and country: Wales, UK. The study began on 20 December 2022, and the study will be completed by 1 August 2023.

### Eligibility criteria

Eligibility criteria will include being over 18 years of age, experiencing mild to moderate symptoms of depression, stress, or anxiety, and being able to read, write and speak English. Prospective participants will be excluded if they are experiencing acute or chronic pain, and/or if they have no psychological symptoms or more severe mental health issues. The rationale for excluding participants with pain is that it may present a confounding variable. That is, if the osteopathic intervention alleviates any pain the participants are experiencing, this may lead to improvements in psychological symptoms. It would, therefore, not be clear whether osteopathy has a more direct influence on mental health outcomes. Screening for mild to moderate psychological symptoms will be conducted using the DASS.

### Interventions

Participants will receive one of four interventions based on osteopathic techniques. All four interventions will consist of a single session lasting approximately 30 min. The interventions are being delivered by two male osteopaths, one with 17 years of practice experience and one with 3 years of practice experience. The interventions will be as follows: (1) articulation and HVT techniques, (2) STM, (3) CST and (4) a combination of all three techniques. A summary of the intervention protocols can be found in table 1.

**Table 1 T1:** Summary of the four intervention protocols and procedures

For all	30 min appointment Clinical findings, intervention, consent and adverse events (separate form to use if they do) recorded in participant individual form	Duration
Articulation/HVT group	Observation+AROM (standing or sitting)+clinical examination for SD (sitting, prone or supine) Techniques: SD found: HVT to the area unless contraindicated (info on BP/HA) No SD found: HVT TSp and ribs Articulation of hips in extension	10 min 20 min
Soft tissue group	Full body, slow and superficial Prone: upper/mid/lower back upper buttocks hamstrings calves Supine: Neck incl. suboccipital muscles Shoulders Pectoral muscles Arms Quadriceps Feet	15 min 15 min
Cranial group	Looking for stiffness, asymmetry and tenderness on: Sacrum Head Dysfunction found: myofascial release technique (10 min/area); if no dysfunction found: functional techniques applied to each area (10 min/area) 3. CV4	10 min 10 min 10 min
Combined group	Observation+AROM+clinical exam for SD HVT TSp Soft tissue upper and lower back prone CV4 and suboccipital release	9 min 7 min 7 min 7 min

AROM, active range of movement; BP, blood pressure; CV4, Compression of the Fourth Ventricle technique; HA, headache; HVT, high velocity thrust techniques; SD, somatic dysfunction; TSp, thoracic spine.

#### Articulation and high-velocity techniques

The AHVT intervention will begin with an examination of the participant to search for somatic dysfunction.^33^ The AHVT intervention will primarily be targeting all areas of the participant’s spine. That is, the cervical, thoracic and lumbar areas, and also the sacroiliac joints. The practitioner will first observe the participant while standing, then will observe active range of movements with the participant in standing and/or sitting positions. Then the practitioner will continue their examination searching first by light and then deeper palpation for signs associated with somatic dysfunction with the participant sitting down or lying prone or supine. This segment of the intervention will be allocated approximately 10 min.

If areas of the spine are found to have somatic dysfunction, then AHVT techniques will be applied to these areas. If no areas of somatic dysfunction are identified in the aforementioned spinal areas, then the practitioner will first focus on applying AHVT techniques to the thoracic spine and rib cage areas, followed by articulation techniques such as hip extension. The application of techniques will be allocated approximately 20 min.

#### STM techniques

The STM intervention will be a full-body massage. The participant will first be in the prone position and the practitioner will massage the upper, middle and lower areas of the back, the upper buttocks, then the hamstrings and calves. This will be approximately 15 min. The participant will then move into the supine position where they will receive massage on their neck, shoulders, pectoral muscles, arms, quadriceps and feet. This will also be allocated approximately 15 min. The literature suggests that slower techniques such as Swedish massage demonstrate effectiveness.^23 28^ There is also evidence that focusing on the upper layers of the skin has psychological benefits.^22^ These techniques will, therefore, be employed here.

#### Craniosacral techniques

This intervention will use CST. This approach targets the cranial muscles and muscles around the central nervous system.^34^ The CST intervention will begin with an examination for somatic dysfunction such as stiffness, asymmetry or tenderness. The body areas focused on will be the soft tissue around the head and sacrum areas which are body areas commonly associated with CST. If areas of dysfunction are identified, then the practitioner will perform myofascial release. If no areas of dysfunction in these areas are identified, the practitioner will first focus on the sacral region and then move on to other areas associated with CST. For sacral and cranial areas, approximately 10 min will be allocated each for 20 min total. The intervention will conclude with fourth ventricle compression (CV4). This technique is performed on the occipital bone. CV4 will be allocated approximately 10 min of the intervention.

#### Combination of techniques

This intervention will be a combination of all three techniques used in the other interventions (COMBO). The intervention will begin with an examination of the participant and checking active and passive range of movement. This examination will be allocated approximately 9 min. Using a combination of treatments, the intervention will consist of: (1) high-velocity techniques applied to the thoracic spine (approximately 7 min), (2) STM to the upper and lower back of the participant in prone (approximately 7 min), and (3) CV4 and suboccipital muscles release (approximately 7 min). This intervention will therefore last approximately 30 min.

### Modifications

In the interest of participant’s safety, certain modifications may be made to the interventions if participants have body areas that are tender or if they present undiagnosed high BP (HBP). This is mostly relevant to the AVHT intervention and COMBO intervention which will have techniques that are of higher force. If a participant in the AVHT or COMBO interventions presents with HBP, neck pain or headaches during the intervention then the practitioner will not work on the cervical spine area and focus on the other spinal regions in the protocol. The justification is that HVT techniques may increase the risk of arterial damage in individuals with HBP.^35 36^

### Adherence

As the intervention only consists of one session, adherence is not necessarily applicable. Instead, a record will be kept of any participants who asked to end the intervention session early.

### Concomitant care

Participants will be asked at preintervention if they are receiving any drug treatment for mental health (eg, antidepressants), or psychotherapy (eg, cognitive behavioural therapy). Participants will not be excluded on this basis, but these will be factored into the main statistical analysis as covariates.

### Outcomes

The primary outcomes are the feasibility and acceptability outcomes (as described in Feasibility and Acceptability section), while the secondary outcomes are the psychological outcome measures (Mental health–Psychological flexibility) and the psychophysiological measures (Heart rate variability–Blood pressure).

#### Feasibility

The feasibility of the recruitment process will be determined by the number of people who respond to the advertisements and the number of people who are eligible/ineligible following the screening process. Specifically, recruitment will be considered feasible if more than 100 people respond and if at least half of the responders are eligible following screening. The feasibility of the measurement tools will first include whether participants have enough time to complete all measures. The feasibility of the questionnaires will also be assessed by any missing data. Additionally, the feasibility of the physiological measurements will be informed by the time taken to set up the equipment. The measures will, therefore, be considered feasible if they can all be completed in the allotted time (approximately 40 min).

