**Methods and analysis:**

This study will be an explanatory mixed-methods design. Participants will be 30 adults who have mild to moderate mental health symptoms and not experiencing any issues with pain. The feasibility and acceptability of the interventions will be the primary outcomes. Secondary outcomes will be physiological measures including heart rate variability, interoceptive accuracy and blood pressure. Psychological outcomes, collected preintervention and postintervention, will also be measured by five standardised questionnaires, which include: (1) the Depression, Anxiety and Stress Scale (DASS); (2) the International Positive and Negative Affect Schedule-Short-Form; (3) Acceptance and Action Questionnaire-II; (4) the Self as Context Scale and (5) and the Multidimensional Assessment of Interoceptive Awareness Version 2. Participants will be randomised to one of four intervention groups and receive a single intervention treatment session. These intervention groups are: (1) high-velocity and articulation techniques, (2) soft-tissue massage, (3) craniosacral techniques, and (4) a combination of these three approaches. Mixed design two (preintervention and postintervention) by the four interventions analysis of covariance models will be used to analyse the quantitative data for each quantitative measure. Participants will also be interviewed about their experiences of the study and interventions and a thematic analysis will be used to analyse this qualitative data. This will aid the assessment of the feasibility and acceptability of the study design.

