### Sample size

The study will aim to recruit 32 participants. This number of participants is generally deemed sufficient for feasibility studies^48^ and would represent approximately 10% of the sample size required in a full trial.^49^ This sample size also falls within what is practical given the available resources.

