## Methods: assignment of interventions

### Allocation

#### Sequence generation

Thirty-two participants will be randomly assigned to one of the four conditions using a computerised random number generator. Permuted block randomisation will be used to ensure that equal numbers of participants are in each condition. The block sizes will not be disclosed to help ensure concealment and prevent any potential prediction of group allocation. This will be conducted by the principal investigator (PI) of the study [name], while the outcome assessor [name] is blinded to this randomisation process.

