#### Implementation

All participants who provide informed consent and who meet the eligibility criteria will be randomised into a study condition (as described in section Sequence generation). The randomiser [name] will not be directly involved in the recruitment or data collection, and instead, the outcome assessor will conduct the recruitment. The list of random numbers that correspond to group allocation will not be revealed to the researcher ([name]) involved in data collection or recruitment. The sealed envelopes will contain a randomisation number and corresponding intervention identity code for the allocation of participants into the intervention groups. The osteopathic practitioner will then be able to open the envelope and determine which intervention is to be delivered on the day the study is conducted.

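### The recruitment criterion is tied neither to the 32 places nor to a counting window, so it may score fast recruitment as not feasible and pass a study that fills few places

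*Protocol article*

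**What the plan says.** All references are to the protocol article.

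- **Feasibility** (a primary outcome) bases recruitment feasibility on "the number of people who respond to the advertisements and the number of people who are eligible/ineligible following the screening process". The rule is then: "Specifically, recruitment will be considered feasible if more than 100 people respond and if at least half of the responders are eligible following screening". It contains no number randomised, no uptake rate and no period over which responders are counted.
- **Sample size**: "The study will aim to recruit 32 participants", with the remark that "This sample size also falls within what is practical given the available resources". The abstract gives a slightly different figure: "Participants will be 30 adults who have mild to moderate mental health symptoms".
- **Sequence generation**: "Thirty-two participants will be randomly assigned to one of the four conditions using a computerised random number generator".
- **Implementation**: "All participants who provide informed consent and who meet the eligibility criteria will be randomised into a study condition". The sentence goes on to refer back to Sequence generation.
- **Recruitment**: consent is signed before the DASS screen, and those found eligible are then invited to the intervention. Table 3 also places consent and screening together at the first time point. The section notes that recruitment has already started.
- **Study setting**: the study runs from 20 December 2022 to 1 August 2023.

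**The concern.** A recruitment criterion should become easier to meet as recruitment becomes easier. Here the first requirement is a minimum number of responders, while the study needs only 32 participants. The better the eligibility and uptake, the fewer responders are needed to fill the places. If the count ends when the places are full, the best recruitment gives the lowest count and may fail the rule.

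The rule is loose in the other direction too. It looks only at responders and eligible people, so it can be met while most places stay empty.

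Feasibility is a primary outcome, this is its only numeric rule for recruitment, and the results are meant to inform a later randomised trial. A verdict pointing the wrong way would misinform that planning.

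A secondary gap follows. Consent precedes screening, so anyone counted as eligible has already consented. If the rule is met, there are more such people than places, and the text does not say what becomes of the surplus.

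**Working it through.** **Inputs**
- N = 32 places (Sample size, Sequence generation).
- Rule: more than 100 responders, so at least 101, with at least half eligible (Feasibility).
- e = proportion of responders eligible. The rule requires at least 0.5; the true value is unknown, so 0.5 to 0.8 is assumed.
- u = uptake, the proportion of eligible people who are randomised. Not given; 0.4 to 1.0 is assumed.
- Condition examined in steps 2 and 3: responder counting stops when place 32 is filled.

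The article derives neither 100 nor 32 from a formula, so there is no calculation to reproduce. The equal-arm statement checks: 32/4 = 8 per arm.

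**Step 1. Smallest passing counts.** 0.5 × 101 = 50.5, so 51 eligible. Then 51 − 32 = 19 eligible consenters beyond the places available.

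**Step 2. Responders needed to fill the places.** Expected number = N/(e × u). Setting this to 100 gives e × u = 32/100 = 0.32; above that product the places fill, in expectation, before 100 people respond. The last column is P(Bin(100, e × u) ≥ 32), the chance that the places are full by the 100th responder. It treats responders as independent and ignores any delay between response and enrolment.

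| e | u | e × u | Expected responders to fill 32 | P(full by 100th) |
|---|---|---|---|---|
| 0.5 | 1.0 | 0.50 | 64 | >0.99 |
| 0.5 | 0.8 | 0.40 | 80 | 0.960 |
| 0.5 | 0.7 | 0.35 | 91 | 0.767 |
| 0.5 | 0.6 | 0.30 | 107 | 0.367 |
| 0.5 | 0.5 | 0.25 | 128 | 0.069 |
| 0.6 | 0.6 | 0.36 | 89 | 0.825 |
| 0.7 | 0.8 | 0.56 | 57 | >0.99 |
| 0.7 | 0.5 | 0.35 | 91 | 0.767 |
| 0.7 | 0.4 | 0.28 | 114 | 0.216 |
| 0.8 | 1.0 | 0.80 | 40 | >0.99 |
| 0.8 | 0.5 | 0.40 | 80 | 0.960 |

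**Step 3. Highest uptake at which 101 responders fit within 32 places.** At the smallest passing counts, 32/51 = 0.627. At higher eligibility, 32/(101 × 0.7) = 0.453 and 32/(101 × 0.8) = 0.396. The ceiling falls as eligibility rises.

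**Step 4. The opposite error.** With 101 responders and 51 eligible the rule is met whatever the uptake. At an assumed uptake of 0.4, 51 × 0.4 = 20.4, so about 20 of the 32 places are filled and recruitment is still scored feasible.

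**Step 5. Sensitivity to the abstract's figure of 30.** The product becomes 30/100 = 0.30. The places fill at 30/0.50 = 60 responders (50% eligible, full uptake) or 30/0.40 = 75 (50% and 80%). The uptake ceiling is 30/51 = 0.588. The conclusion is unchanged.

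**The case against.** The strongest reply is that the stopping condition is not in the text. Sample size and Sequence generation fix how many are recruited and randomised; they do not say when responses cease to be counted. Responses come through posters and online links, each participant then needs an in-person visit, and responses could keep arriving while visits are booked. If counting simply continues, higher eligibility can only help the rule. This stands. A reader might infer that easy recruitment is bound to be scored not feasible, but the documents do not support that: the count may continue, and eligible people are only invited, so full uptake cannot be presumed. With half eligible and uptake of about 63% or less, more than 100 responders can be reached even with stopping at 32.

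A second tempting reading is that Implementation flatly contradicts Sequence generation by randomising every eligible consenter. It does not, because the same sentence refers back to the section that states thirty-two. What remains is a gap: nothing says what happens to eligible consenters beyond the thirty-second.

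Third, a pool-size criterion is defensible in itself. Sample size describes 32 as about 10% of a full trial, implying roughly 32/0.10 = 320, and it is reasonable to ask whether advertising reaches enough people for that. This also stands, but such a criterion needs a stated counting period to be interpretable.

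Finally, no stop/go decision is attached to the rule, and both underlying counts are to be assessed, so a study that filled quickly would be visible to a careful reader. That lowers the severity without mending the rule.

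**Conclusion.** The point holds as a conditional defect of moderate severity. The rule is anchored neither to the 32 places nor to a counting period. If counting stops when the places are full, it fails in expectation once eligibility times uptake passes about 0.32, a region that includes plausible good recruitment. Independently of any stopping assumption, it can be met with far fewer than 32 randomised, because that number is not part of it.

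The first part rests on two things that the article does not give: that counting ends at 32, which is suggested but unwritten, and the uptake among eligible people, for which only a range can be shown. The second part and the gap over surplus consenters follow from the text as it stands.

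**What to change.** In **Feasibility**, choose one of two forms:
1. Count responders and eligibility over a fixed advertising window that runs regardless of when the places fill.
2. Judge recruitment by whether 32 are randomised by the end date in Study setting, reported with the eligible/screened and randomised/eligible proportions.

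Replacing 100 with 64 is not enough. With 70% eligible and 80% uptake the places fill at 32/(0.7 × 0.8) = 57 responders, and with 80% eligible and full uptake at 32/0.8 = 40. Both would fall short of 64, so the defect would stay.

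In **Implementation**, say that the first 32 eligible, consenting participants are randomised, and that later eligible responders are counted but not randomised.

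Record the change as a dated amendment under **Protocol amendments**, ideally before responder counts are reviewed. The cost is about two sentences and no extra participants. The real drawback is that a primary-outcome criterion changes after recruitment has begun, which the final report should disclose.

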### Participant timeline

See table 3 for the participant timeline.

**Table 3 T3:** Participant timeline

Activity/ assessment	Approx. time to complete	T_-1_ Prestudy screening/ consent	T_0_ Prestudy randomisation	T_1_ Preintervention	T_2_ Intervention	T_3_ Postintervention tests	F_1_ Follow-up 1 week
Informed consent	5 min	X					
Screening with DASS	5 min	X					
Randomisation	15 min		X				
Baseline assessment— questionnaires	15 min			X			
Baseline assessment— physiological	15 min			X			
Intervention	30 min				X		
Postintervention questionnaires	15 min					X	
Postintervention physiological	15 min					X	
Telephone interview	30 min						X

DASS, Depression Anxiety Stress Scale; F, follow-up; T, timepoint.

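### The recruitment criterion implies at least 51 eligible people in a trial that randomises 32, never tests whether 32 were randomised, and sits beside a 40-minute limit not tied to Table 3

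*Protocol article*

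**What the plan says.** The Outcomes section makes feasibility and acceptability the primary outcomes. The Feasibility section gives two numerical rules. For recruitment: "recruitment will be considered feasible if more than 100 people respond and if at least half of the responders are eligible following screening". For the measures, they will "be considered feasible if they can all be completed in the allotted time (approximately 40 min"; the sentence before this makes equipment set-up time part of the assessment, without giving minutes.

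On numbers, the Sample size section states: "The study will aim to recruit 32 participants". The Sequence generation section agrees: "Thirty-two participants will be randomly assigned to one of the four conditions using a computerised random number generator". The abstract differs: "Participants will be 30 adults who have mild to moderate mental health symptoms".

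On flow, the Recruitment section has people sign consent, then complete the DASS screen, and then, if eligible, be invited to take part. The Implementation section states: "All participants who provide informed consent and who meet the eligibility criteria will be randomised into a study condition".

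Table 3 allots 15 min to questionnaires and 15 min to physiological measures before the intervention, and the same again afterwards (the "Postintervention questionnaires" row and the row below it). It has no row for set-up.

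**The concern.** The recruitment rule counts responders and eligible people. The design fixes the number randomised and says that all consenting, eligible people are randomised. A rule demanding many more eligible people than there are places does not sit with that design. It also leaves out what a feasibility study most needs to know about recruitment: whether the places were filled, and what share of eligible people reached randomisation. A stated primary criterion could then give the wrong label in both directions. The time limit raises a similar question, because it refers to an allotted time that the timeline table does not show.

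**Working it through.** **Inputs.** Over 100 responders, so at least 101, and an eligible share of at least 50% (Feasibility). 32 randomised over four equal arms (Sample size, Sequence generation, Trial design). Consent before the DASS screen (Recruitment). All consenting, eligible people randomised (Implementation). Measurement rows of Table 3: screening DASS 5 min; questionnaires 15 min and physiological measures 15 min, each on two occasions.

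**Sample size.** No power inputs are given. The 32 rests on convention, practicality and the statement that it "would represent approximately 10% of the sample size required in a full trial", which implies 32 / 0.10 = 320. So 32 can be neither reproduced nor refuted by a formula. It splits evenly (32 / 4 = 8 per arm); the abstract's 30 does not (30 / 4 = 7.5).

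**Recruitment rule: smallest passing result**
- Eligible: 101 × 0.5 = 50.5, so 51.
- Eligible people not randomised if 32 is held: 51 − 32 = 19, and 19 / 51 = 37%.
- Only those who have consented are screened, so all 51 have consented. Under the Implementation section all 51 would be randomised; under Sequence generation, 32 would be.

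**If screening stopped at the 32nd eligible person** (an assumption; the protocol does not say so)
- With 101 responders, the eligible share is at most 32 / 101 = 31.7%, below the 50% required.
- With a share of at least 50%, there are at most 32 / 0.5 = 64 responders, below the 101 required.

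**How the rule labels plausible results**

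| Responders | Eligible | Randomised | Label |
|---|---|---|---|
| 64 | 32 (50%) | 32 | infeasible |
| 40 | 32 (80%) | 32 | infeasible |
| 101 | 51 (50.5%) | any number, however small | feasible |

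**Time limit**
- One occasion: 15 + 15 = 30 min. Both: 2 × 30 = 60 min. Both plus the screening DASS: 65 min.
- All possible sums of the measurement rows are 5, 15, 20, 30, 35, 45, 50, 60 and 65 min. None is 40.
- Reaching 40 from the table needs a non-measurement row, for example consent 5 + screening DASS 5 + baseline 15 + 15.
- If set-up is additional and takes 10 min per occasion (an assumption), 30 + 10 = 40. A set-up of 5 to 15 min gives 35 to 45 min.
- If the limit covers both occasions, the schedule exceeds it by 60 − 40 = 20 min.

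**The case against.** A reader might infer that the two parts of the recruitment rule can never hold together. The document does not support that. It nowhere says that advertising or screening stops at 32. Entry is by an online link and consent form, so responders can accumulate beyond the places available. Eligible people are invited, so some may decline. A result of 101 responders, 51 eligible and 32 randomised is arithmetically possible. Requiring demand well above 32 may also be deliberate, given that 32 is put at about a tenth of a full trial. This defeats any claim of impossibility. It does not remove the conflict with the Implementation section, supply a rule for the surplus, or make the criterion test randomisation.

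A reader might also infer that the 40-minute limit is a proven error, or bound to fail. Neither follows. The limit is approximate, set-up time is named in the preceding sentence, and 30 min of measures plus about 10 min of set-up is a natural reading. Failure by design arises only if 40 min spans both occasions, which is the less natural reading. What stands is that the occasion and the place of set-up are not stated.

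Nor does the document say that this criterion decides whether a full trial follows. The abstract's Discussion says that the results will help to inform one; there is no stop/go rule, and acceptability is also primary.

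Finally, 20 December 2022 and 1 August 2023 are given as study start and completion. They are not a recruitment window, and no planned recruitment rate can be read from them.

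**Conclusion.** The point holds in a limited form. Meeting the recruitment criterion requires at least 51 eligible people, which cannot be squared with both 32 randomised and randomisation of all who consent and are eligible. With 32 held, it can be met only if screening runs on after the places are filled, or if enough eligible people are lost before randomisation; either way at least 19 of 51 are not randomised, and the plan does not say how they are handled. Apart from that conflict, the criterion misclassifies: it fails full recruitment from 64 or 40 responders and can pass with few randomised. These results rest only on the protocol's own figures and on the stated order of consent and screening.

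The 40-minute limit is undefined rather than shown to be wrong. The 30 in the abstract against 32 in the body is a plain but minor contradiction. All of this can be corrected in wording, and is worth correcting because the criterion is a stated threshold for a primary outcome.

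**What to change.** 1. Judge recruitment on randomising 32 within a stated recruitment period that ends early enough for the one-week interview to be done before study completion on 1 August 2023.
2. Report the proportion of responders who are eligible and the proportion of eligible people randomised, each with a 95% CI. Drop the minimum responder count as a pass condition, or keep it as a descriptive figure.
3. State when screening stops and how eligible people beyond 32 are handled, and bring the Implementation section into line.
4. State that the 40-minute limit applies per occasion and whether it includes equipment set-up, and reconcile it with the 30 min in Table 3.
5. Change the abstract's 30 to 32.

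No new data are needed: responders and eligible people are already to be counted, and the number randomised is known. The cost is more than wording in one respect. Recruitment has begun, so changing a primary threshold is a mid-study change. It should be dated, listed and justified under the Protocol amendments section, with a statement of which recruitment counts were known at the time.
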